### Inclusion criteria

2.6

Patients must fulfill all the following criteria to be eligible for inclusion in this study:

(1) Age: 18–75 years old. (2) Patients with histologically proven cutaneous squamous cell carcinoma or basal cell carcinoma. (3) Without distant metastasis. (4) Without any other medical condition or laboratory value that would, at the discretion of the investigator, preclude the patient from participation in this clinical investigation. (5) Without any serious underlying medical condition that could interfere with study treatment and potential adverse events. (6) The Eastern Cooperative Oncology Group (ECOG) score: 0–2. (7) Patients requiring radiotherapy treatment according to the dermato‐oncology tumor board: standard treatment is ineffective, patients who are either medically inoperable or refuse to surgical resection, and/or anatomical locations where surgery can compromise function or cosmesis. (8) The disease progression affects patients’ quality of life. (9) T1‐T2 N0 lesions with a small (T1; lesion ≤ 2cm in diameter) or large (T2; 2cm < lesion ≤ 4 cm) volume (the Union for International Cancer Control (UICC) Classification of Malignant Tumours, 8th Edition); the size of the treated lesion should be ≤ 3.5 cm thick (caliper‐based measurement). (10) Clinically acceptable treatment plan with electron FLASH‐RT. (11) Treatment associated side effects are limited and controllable. (12) Life expectancy ≥ 3 months (in the judgement of the investigator). (13) A FLASH‐RT team consisting of 4 radiation oncologists, 3 radiation physicists, and 1 dermatologist should be established prior to radiotherapy. (14) No antibiotics, hormones, immunosuppressive drugs, probiotics, etc. were used within 1 month prior to treatment. (15) Patients who can comply with the protocol. (16) Sign the phase I study informed consent form.

### Exclusion criteria

2.7

Patients who meet any of the following criteria will be ineligible for this study: (1) Patients who are pregnant or nursing. (2) Patients with known contraindications to radiation. (3) Concomitant use of systemic oncological treatment for a cancer other than the skin cancer. (4) Concomitant auto‐immune disease with skin lesions. (5) Patients who will receive cytotoxic chemotherapy within 1 week prior to or 1 week following their planned radiation treatment. (6) Previous radiotherapy in the treated area. (7) Concomitant use of radio‐sensitizer drug. (8) Patients who are unable to comply with study requirements or follow‐up schedule. (9) Patients who combined with cognitive disorders not compatible with the signature of informed consent or other impairment that may compromise compliance with the requirements of the study. (10) Patients with symptomatic pneumonitis at the time of screening, or a history of symptomatic radiation pneumonitis. (11) Patients enrolled in any other clinical studies the investigator believes to conflict with this clinical investigation.

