### Objectives

2.1

The primary objective of this study is to evaluate the safety and acute radiation‐related toxicity (≤ 90 days) in patients with localized superficial skin tumor after FLASH‐RT using National Cancer Institute (NCI) Common Terminology Criteria for Adverse Events (CTCAE v5.0).^12^

The secondary objectives are as follows: 1. To evaluate late toxicity (> 90 days) of FLASH‐RT in patients with localized superficial skin tumor from time of radiation. 2. Estimate treatment efficacy of FLASH‐RT with the Response Evaluation Criteria in Solid Tumors (RECIST) criteria (v1.1) after radiotherapy.^13^

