### Study design

2.2

This is a single institution, prospective, single arm safety study to evaluate the feasibility and safety of electron FLASH‐RT in patients with localized superficial skin tumor. Patients with localized superficial skin tumor will be considered for enrolling in this phase I study. All the eligible patients will be discussed at multi‐disciplinary meeting. Patients will be formally recruited and managed by members of the FLASH‐RT team. The treatment protocol is shown in Figure 1.

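### The exclusion criteria leave systemic treatment of the treated skin cancer open, so in patients who receive it response, and to a lesser degree acute toxicity, cannot be separated from the FLASH-RT effect

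*Protocol article*

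**What the plan says.** Four eligibility items in the protocol article bear on systemic treatment.

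- Section 2.7, exclusion 3: "Concomitant use of systemic oncological treatment for a cancer other than the skin cancer".
- Section 2.7, exclusion 5: "Patients who will receive cytotoxic chemotherapy within 1 week prior to or 1 week following their planned radiation treatment".
- Section 2.7, exclusion 7: "Concomitant use of radio‐sensitizer drug".
- Section 2.6, inclusion 14: "No antibiotics, hormones, immunosuppressive drugs, probiotics, etc. were used within 1 month prior to treatment".

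Section 2.2 describes the design: "This is a single institution, prospective, single arm safety study to evaluate the feasibility and safety of electron FLASH‐RT". In section 2.1 the primary objective is to "evaluate the safety and acute radiation‐related toxicity (≤ 90 days) in patients with localized superficial skin tumor after FLASH‐RT", graded by CTCAE v5.0. A secondary objective begins "Estimate treatment efficacy of" and names FLASH-RT, measured by RECIST v1.1. Section 2.5 has toxicity recorded weekly for three months and clinic visits with imaging every three months for two years. Section 2.8 gives 12 patients and descriptive analysis. Section 2.6 limits entry to T1-T2 N0 lesions without distant metastasis.

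**The concern.** Exclusion 3 is qualified by which cancer is being treated, and the qualification removes the one cancer that matters most for the endpoints. A patient on systemic treatment for the lesion about to be irradiated does not meet exclusion 3. Exclusion 5 has no such qualification, but it covers one drug class for a short period.

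The trial has no comparator. If a patient within the rules receives another active treatment for the same tumour, nothing in the design shows how much of a RECIST response came from FLASH-RT. A skin reaction within the 90-day window may likewise be caused or altered by the other treatment. The abstract says that favourable results would lead to a phase II efficacy trial, so the response figure will be used beyond this study.

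**Working it through.** **Step 1. Read the four criteria together.** The question is what each one bars when the drug is given for the treated skin cancer.

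| Criterion | Drugs covered | Period covered | Covers the index tumour? |
|---|---|---|---|
| Exclusion 3 | Any systemic anticancer drug | Concomitant | No, other cancers only |
| Exclusion 5 | Cytotoxic chemotherapy | 1 week before to 1 week after radiation | Yes |
| Exclusion 7 | Radiosensitisers | Concomitant | Yes |
| Inclusion 14 | Antibiotics, hormones, immunosuppressants, probiotics and an open-ended remainder | 1 month before treatment | Yes for the listed drugs; anticancer drugs are not named |

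Two things remain allowed for the index tumour:

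- non-cytotoxic systemic treatment, unless the drug counts as a radiosensitiser or falls under inclusion 14 beforehand;
- cytotoxic chemotherapy from the second week after radiation.

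**Step 2. How much of the toxicity window is open to chemotherapy.** Counting the 90 days from the end of radiation (an assumption), exclusion 5 covers 7/90 = 7.8% and leaves 83/90 = 92.2%. Chemotherapy started in the second week would also come before the first three-monthly clinic visit.

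**Step 3. Weight of one patient.** With N = 12 (section 2.8), each affected patient is 1/12 = 8.3 percentage points of any reported rate. Two are 2/12 = 16.7 points and three are 3/12 = 25.0 points.

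**Step 4. Chance that it arises at all.** The article does not say how often such treatment is used, so a range is assumed. With use probability q, independent between patients, P(at least one of 12) = 1 − (1 − q)^12.

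| Assumed q | Expected patients, 12q | P(at least one) |
|---|---|---|
| 2% | 0.24 | 21.5% |
| 5% | 0.6 | 46.0% |
| 10% | 1.2 | 71.8% |
| 20% | 2.4 | 93.1% |
| 30% | 3.6 | 98.6% |

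At low use it may never occur; at 10% or more, at least one affected patient is likely.

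**Step 5. Effect on the safety statement.** Suppose no event of a given kind is seen. The exact one-sided 95% upper bound is 1 − 0.05^(1/n). For n = 12 it is 22.1%. If two patients had to be set aside, n = 10 gives 25.9%. The loss of precision is 3.8 points, which is modest.

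The article gives no error rate, power or target rate behind the 12 patients, so there is no stated figure to reproduce, and the point does not depend on one.

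**The case against.** The strongest case on the other side has five parts.

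*The exposure is probably rare.* Entry is limited to T1-T2 N0 disease without metastasis. This stands. A reader might infer that no response or toxicity in the trial can be attributed to FLASH-RT. The documents do not support that: only patients who actually receive such treatment are affected, and they may be few or none.

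*Toxicity is already framed by cause.* The primary objective concerns radiation-related toxicity, and section 2.5 speaks of radiation-induced events. This stands in large part. Attribution is built into the endpoint, and a reaction confined to the treated field may still be assignable. Judging cause is harder when a second agent is present, so the problem is reduced for toxicity and not removed. RECIST response has no such causal filter.

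*Other criteria restrict drugs.* This is correct, and exclusion 7 and inclusion 14 have to be counted. Step 1 shows what they leave open. A reader might also infer that inclusion 14 and exclusion 5 contradict each other, since one looks back a month and the other a week. They do not. A patient must meet every inclusion criterion and no exclusion criterion, so the two apply cumulatively and the longer look-back governs where both fit.

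*This is an article, and the full protocol may contain a section on concomitant treatment.* That is so, and the absence of such a section here is not the point. The point rests on what exclusions 3 and 5 say.

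*The sizes are assumed.* They are. The documents give no frequency of systemic treatment, so Step 4 is a range and not an estimate. The weight of 1/12 per patient holds in any 12-patient trial; it shows what one affected patient would cost, not how many there will be.

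**Conclusion.** The point holds in a limited form. As worded, the criteria allow non-cytotoxic systemic treatment of the treated tumour, and chemotherapy for it from the second week after radiation. In a single-arm trial, RECIST response in a patient so treated cannot be separated from the effect of FLASH-RT; for acute toxicity the same applies to a lesser degree. Each such patient accounts for 8.3 percentage points of a reported rate. How many there will be is unknown: under assumed use of 2% to 30% the expected number runs from 0.24 to 3.6 of 12.

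The conclusion assumes that exclusion 3 is applied as written and that no unseen section of the full protocol overrides it. It does not make the trial uninterpretable. It is a worthwhile correction at low cost, because the stated exclusion does not match the aim of describing the toxicity and efficacy of FLASH-RT itself.

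**What to change.** 1. **Eligibility.** Bring exclusions 3 and 5 into line with the trial's aim by removing the index-tumour carve-out from exclusion 3, so that patients already on concomitant systemic anticancer treatment for the treated skin cancer at entry are not enrolled. The windows in inclusion 14 and exclusion 5 need no change on this account.

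2. **Analysis rule for treatment started later.** Do not restrict care. State in advance that:
   - a response first seen after such treatment started is not credited to FLASH-RT;
   - the patient stays in the safety set;
   - toxicity arising after the start is reported separately.

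   This requires the start date of any such treatment to be recorded.

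**Cost.** One edit to the eligibility list and a short analysis rule. Accrual should fall only slightly, given the stage of disease admitted. The reported response rate may be slightly less favourable: with imaging every three months, a genuine FLASH-RT response that is first documented after other treatment began would not be credited.

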### Statistical analysis and sample size

2.8

Descriptive statistics will be utilized to record baseline and clinical pathological parameters. The sample size of our study was 12 patients, and data analysis will be conduct once the study has been completed.

### Safety stopping rules

2.9

FLASH‐RT will be delayed until toxicity improves to less than grade 2 in case any of the following adverse events: White blood cell count < 1.5 × 10^9^ cells/L; Absolute neutrophil count < 1.0 × 10^9^ cells/L; Platelets < 40 × 10^9^ cells/L; ≥ grade 3 non‐hematological toxicity.

If skin infection is observed in the tumor area with fever over 38.5°C, FLASH‐RT will be delayed until complete recovery. And FLASH‐RT will be terminated if the patient does not recover within 2 weeks.

### Ethics and dissemination

2.10

This study was conducted in accordance with the ethical standards of the World Medical Association Declaration of Helsinki. The study was approved by the Medical Ethics Committee of Henan Cancer Hospital & the Affiliated Cancer Hospital of Zhengzhou University (2023‐KY‐0148‐003). The written informed consent was approved by the review board of our institution. All patients or an authorized representative, will be informed of the nature of the study and will provide the written informed consent. The risks, benefits, and details of each intervention will be discussed by the radiation oncologists with all patients enrolled on this protocol. This study has been registered at Chinese Clinical Trial Registry.gov (ChiCTR2400080935). The results of this trial will be submitted to a peer‐reviewed journal for publication. The abstract will be presented on international conferences.

Besides, the group from Cincinnati Children's Proton Therapy Center performed proton FLASH‐RT (NCT04592887) for the palliative treatment of painful bone metastases, a total of 10 patients was included and a single dose of 8 Gy was delivered.^11^ Acute treatment‐related toxicities of FLASH‐RT including grade 1 edema, erythema, fatigue, pruritus, skin hyperpigmentation and grade 2 extremity pain. Long term toxicity of grade 1 skin discoloration was only observed in 1 patient. Overall, the adverse events of proton FLASH‐RT were mild and consistent with conventional RT. This group is conducting another clinical trial to assess toxicities of FLASH‐RT (NCT05524064) and pain relief in patients with painful thoracic bone metastases.

In conclusion, radiation oncology is on the way to the era of FLASH‐RT. The present protocol will evaluate the toxicity of electron FLASH‐RT for the treatment of localized superficial skin tumor. If the results show that FLASH‐RT is safe and feasible, it warrants further investigation in the future.

## ETHICAL STATEMENT

This study was conducted in accordance with the ethical standards of the World Medical Association Declaration of Helsinki. The study was approved by the Medical Ethics Committee of Henan Cancer Hospital & the Affiliated Cancer Hospital of Zhengzhou University (2023‐KY‐0148‐003). The written informed consent was approved by the review board of our institution. All patients or an authorized representative, will be informed of the nature of the study and will provide the written informed consent.

## Data Availability

Datasets and other files generated, analyzed, or processed in this study are available upon request from the corresponding author.
